
#### Analytical strategy for integrating multi‐omics data processing of biological samples

Fecal to assess the role of early‐life microbiome in the development of health, and how gut microbiome dysbiosis could contribute to disease development. Meanwhile, feacal calprotectin, metabolomics, or sweeteners could be assessed using fresh stool. Breast milk samples will be analyzed using untargeted and targeted metabolomics sequencing for their human milk oligosaccharides content and small molecules. Umbilical cord blood will be prepared to evaluate the transfer of maternal metabolites and immune molecules to the infant, and how it may establish and maintain health development in children. Vaginal swabs and maternal oral samples are collected to investigate the sources of neonatal gut microbiome. Air swabs of the hospital room during delivery are collected for further analysis of environmental exposure to the neonatal microbiome. Nasopharyngeal swabs from infants are collected to investigate the relationship between nasopharyngeal microbiomes and the development of their physical health and respiratory disease. The hair and nail samples are collected for further DNA analysis, extending the host genomic analysis from single genes to genome‐wide analysis to investigate how host genetics shape early life microbiota development. Furthermore, collecting and storing cord blood and placentas grants us the opportunity to delineate how human genetics influence early life microbiome composition.

For other body sites with 16S/ITS data, ASV‐level transmission rates will be calculated with the stool metagenomic to match the corresponding resolution. Personal mother‐infant transmission events will be assessed by calculating narrow‐sense heritability (h2 defined as the proportion of variance in microbial presence/absence profiles explained by additive genetic effects, which will also capture the shared exposure [38]. These data will help to answer which body site contributes to the infants' gut microbiome. And whether the proportion of the microbiome sourced from other body sites, besides the gut, affects the health and disease of infants.

Stool metagenomic and metabolomic data, skin/nasopharyngeal swab/breastmilk 16S rRNA amplicon sequencing data, and blood epigenetic data will be considered as different dimension data, and therefore the multi‐omics models will be applied. To deal with such high‐dimensional omics data, our analytical strategies varied. For those samples with omics assessments, multiblock Projection to Latent Structures will be conducted for either unsupervised or supervised analysis or Canonical Correlation Analysis will be employed according to the study aims (for classification or regression).

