**Figure 1 imo270068-fig-0001:**
[figure not shown]
Overview of the MOMMY cohort. (A) The families enrolled are followed prospectively from pregnancy, delivery, and postnatal months 1, 2, 6, 12, 18, and years 2 to 7. (B) The demographics of subjects in the 3 MOMMY study sites.

The primary objective of the MOMMY cohort is to study early‐life mother‐to‐infant microbial transfer and the effect of such microbial colonization on infants' later‐life development and responses.

The secondary objectives include:
(1)to establish a metagenomics platform and framework to study vertical microbial transmission from mothers to babies,(2)to investigate the changes in the microbiome in infants born to mothers with different health conditions,(3)to define the healthy early life microbiome in the first 1000 days in the Chinese population,(4)to study the correlation and/or causation between the microbial transmission patterns and the short and medium‐term health and disease of babies, including neurodevelopment, growth, allergies, and infectious diseases.

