#### Strain resolution techniques to study microbiome transmission

Strain characterization will be performed using StrainPhlan based on pre‐processed metagenomic data to further characterize the single‐nucleotide variants (SNVs) [39]. Strain transmission rates will be calculated as the number of strain transmissions between two samples divided by the number of shared species profiled by StrainPhlAn (number of transmission strains/number of shared species). Strain acquisition rates by the offspring will be defined as the proportion of strains profiled in the offspring transmitted from mothers, thus putatively originating from them. Species transmissibility will be defined as the number of strain transmission events detected for a species divided by the total potential number of strain transmission events based on the presence of a strain‐level profile by StrainPhlAn [40]. We will mainly assess strain transmission across the following modes: related mother‐infant (defined between mothers and their offspring). The transmission between mother‐infant pairs will be evaluated using mothers' stool samples during late pregnancy, which is the closest to delivery time. Further, we will perform de novo assembly and Metapi will be applied [41]. Briefly, the high‐quality reads will be assembled using MEGAHIT [42]. To facilitate genome recovery, reads of samples from the same infants collected at multiple time points will be co‐assembled. Reads will be mapped back to the resulting contigs using minimap with default parameters [43]. Binning of contigs into metagenome‐assembled genomes (MAGs) will be done using two automatic binning programs: MetaBAT2 and VAMB [44, 45]. High‐ (completeness > 90% and contamination < 5%) or medium‐quality (completeness > 50% and contamination < 10%) MAGs (MAGs) will be identified by CheckM, consistent with Minimum Information about a Metagenome‐Assembled Genome (MIMAG) standard [46, 47]. The taxonomic assignment of these representative bacterial species‐level MAGs will be performed by GTDBTk based on the GTDB database [48, 49]. InStrain will be applied to sensitively detect shared microbial strains based on MAGs of species [50]. Apart from the stool samples, the placenta sample and one air swab sample collected during delivery will help to disentangle the true microbial transfer effects from the shared environment between mother and infant.

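### Narrow-sense heritability is used to assess personal mother-infant transmission at the 16S/ITS body sites, which it cannot do; the strain rates carry no background term, and the stated safeguard does not supply one

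*Protocol article*

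**What the plan says.** The objectives, given after Figure 1, state: "The primary objective of the MOMMY cohort is to study" early-life mother-to-infant "microbial transfer and the effect of such microbial colonization on infants' later" development and responses.

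Two later sections say how transfer will be measured.

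- **Analytical strategy for integrating multi-omics data.** One paragraph covers body sites other than the gut, where 16S/ITS data are used. It plans ASV-level transmission rates. It then says that personal mother-infant "transmission events will be assessed by calculating narrow"-sense heritability, with "h2 defined as the proportion of variance in microbial presence/absence profiles explained by additive genetic effects, which will also capture the shared exposure". The inference to be drawn follows at once: "These data will help to answer which body site contributes to the infants' gut microbiome". The paragraph goes on to ask whether the share sourced from sites other than the gut affects infant health.
- **Strain resolution techniques.** This section defines a strain transmission rate (transmitted strains over shared species), a strain acquisition rate and a species transmissibility, and adds inStrain. It uses maternal stool from late pregnancy. On pair types it says "We will mainly assess strain transmission across the following modes: related" mother-infant pairs, and it lists no other mode. It closes by saying that the placenta sample and one air swab taken at delivery "will help to disentangle the true microbial transfer effects from the shared environment between mother and infant".

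**The concern.** Heritability answers a different question from transmission. It describes how much of the variation across a population goes with additive genetic differences. It does not attach to a pair, a taxon in that pair, or a direction of movement between body sites. The article also says that its version takes in shared exposure. A high value at a body site could therefore reflect genes, a common environment or actual transfer, and nothing in the stated rule tells these apart. Yet the result is meant to say which body site contributes to the infant gut.

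The strain rates raise a separate and milder problem. A strain that circulates widely will be found in both members of some pairs without having passed between them. A rate computed in related pairs counts those matches as transmission unless a background rate is taken off. The article says that two samples will help to separate transfer from shared environment, so a reader may believe the matter is settled.

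Both measures feed the primary objective, the heritability through the body-site question and the strain rates through stool transfer.

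**Working it through.** The article gives no figure for the transmission analysis, so there is none to reproduce. All numerical inputs below are assumptions chosen to show how the measures behave.

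**1. What heritability picks up in mother-infant pairs.** Let VA be the additive genetic variance, VC the shared exposure variance and VT the variance due to true transfer, with total variance 1. Mother and child share half the additive variance, so

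Cov(mother, infant) = VA/2 + VC + VT, and estimated h2 = 2 × Cov / Var.

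| VA | VC | VT | Calculation | Estimated h2 |
|---|---|---|---|---|
| 0 | 0.2 | 0 | 2 × 0.2 | 0.40 |
| 0 | 0 | 0.2 | 2 × 0.2 | 0.40 |
| 0 | 0.1 | 0.1 | 2 × (0.1 + 0.1) | 0.40 |
| 0.2 | 0.1 | 0 | 2 × (0.1 + 0.1) | 0.40 |
| 0.4 | 0 | 0 | 2 × 0.2 | 0.40 |

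Simulating 200,000 pairs for the first three rows gave 0.402, 0.403 and 0.401. Five different mechanisms, two of them with transfer and three without, give the same value.

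**2. Whether another estimator would help.** The article does not name the estimator. Suppose a kinship-based method did isolate the additive genetic part. The result would then be a genetic quantity and still not transfer. If it does not isolate that part, it contains shared exposure, as the article says. Neither case yields a measure of transmission.

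**3. Behaviour for a fixed transfer probability.** Suppose a mother who carries a taxon passes it on with probability 0.6, and the infant has no other source. With maternal prevalence p,

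2r = 2 × 0.6 × √(p(1 − p)) / √(0.6p(1 − 0.6p)).

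- p = 0.5: 0.6 / √(0.3 × 0.7) = 1.31, outside the range of a heritability.
- p = 0.99: 1.2 × √0.0099 / √(0.594 × 0.406) = 0.24.

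Under this estimator, which is an assumption, the same transfer gives very different values, and very common taxa pull the value down.

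**4. Strain rates without a background term.** Let p0 be the sharing rate expected without transfer and t the true transfer. Then

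observed = p0 + (1 − p0) × t, so t = (observed − p0) / (1 − p0).

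| Observed | p0 | t | Share of observed that is background, 1 − t/observed |
|---|---|---|---|
| 30% | 0% | 30% | 0% |
| 30% | 5% | 0.25/0.95 = 26.3% | 12% |
| 30% | 10% | 0.20/0.90 = 22.2% | 26% |
| 30% | 20% | 0.10/0.80 = 12.5% | 58% |
| 20% | 20% | 0% | 100% |

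**5. Whether the stated safeguard supplies p0.** The biological samples section says that the delivery air swab comes from the ward for vaginal births and from the operating theatre for cesareans, so its location follows delivery mode. It says nothing of home, diet or community. The placenta is not a sample of the surroundings. Neither sample shows how often an infant shares a strain with a mother who is not its own, which is what p0 requires.

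**The case against.** The strongest reply is about scope, and much of it stands.

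- A reader might infer that heritability is the measure of the primary objective and that the objective therefore cannot be met. The article does not support that. Heritability appears only in the paragraph on 16S/ITS body sites, beside ASV-level transmission rates. Transfer in stool rests on strain measures that do not use it.
- A reader might also infer that strain sharing is assessed only in related pairs. The text says mainly. The article condenses a fuller protocol, which may hold an unrelated-pair comparison, so its absence here is not by itself an error.
- Common taxa do not inflate heritability. A taxon that everyone carries adds no covariance, and step 3 of the working shows the value falling at high prevalence. The inflation from common strains applies to the uncorrected strain rates.
- Some protection exists. Late-pregnancy maternal stool predates any shared postnatal household, infant stool is taken from birth, and the article calls maternal origin putative. Table 1 also lists air swabs at paediatric clinics during months 1 to 12, though these do not measure home exposure.
- It is tempting to say that mother-infant minus father-infant sharing isolates maternal transfer. It does not: it contrasts two household members with different contact. Table 1 also shows no father skin or nasopharyngeal samples, so the contrast is missing at most of these sites.

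What the reply leaves untouched is that the article assigns heritability to personal transmission events and draws a conclusion about source from it, and that it credits two samples with a separation they do not perform.

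**Conclusion.** The point holds in limited form. At the 16S/ITS body sites, a population variance ratio that mixes genes and shared exposure cannot identify personal transmission events or a source site. This follows from the article's own definition and needs no assumed number. Disclosing that shared exposure is included does not repair it, because the conclusion about source is still drawn.

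For the strain measures the conclusion is narrower. As described, the rates have no background term, related pairs are the only mode listed, and the placenta sample and single air swab do not estimate background sharing. How much this matters depends on rates that the article does not give. The 12% to 58% background share at 30% observed sharing, and the common value of 0.40, illustrate the mechanism under assumed inputs and do not predict what MOMMY will find. The material does not show that the primary objective is out of reach.

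**What to change.** 1. Stop using heritability as a measure of transmission. If it is kept, call it familial resemblance and draw no conclusion about source from it.
2. For ASVs at each body site and for strains in stool, report sharing in own-mother pairs against sharing in unrelated mother-infant pairs matched on study site, infant age and delivery mode. Test the difference by permuting mothers within those strata.
3. State what this does and does not remove. It takes out background sharing of common strains. It leaves household sharing, because unrelated mothers do not live with the infant. The transmission claim should therefore rest on the earliest infant samples paired with late-pregnancy maternal samples. Table 1 lists breast milk only from birth onward, so that ordering is not available for milk, and this should be said.
4. Father-infant pairs may serve as a supporting contrast for household sharing, for stool (pregnancy and 6 months in Table 1) and mouth rinse only, without a claim that they isolate vertical transfer. Table 3 lists 1,059 + 503 + 102 = 1,664 fathers and 1,465 + 528 + 107 = 2,100 mothers.
5. Describe the placenta sample and the delivery air swab as supplementary, or state the analysis that will use them.

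The cost is extra computation on data the cohort already holds. Matching will be coarser in Kunming, with 107 mothers in Table 3. Reported transmission rates will probably be lower.

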#### Strain resolution techniques to study microbiome transmission

Strain characterization will be performed using StrainPhlan based on pre‐processed metagenomic data to further characterize the single‐nucleotide variants (SNVs) [39]. Strain transmission rates will be calculated as the number of strain transmissions between two samples divided by the number of shared species profiled by StrainPhlAn (number of transmission strains/number of shared species). Strain acquisition rates by the offspring will be defined as the proportion of strains profiled in the offspring transmitted from mothers, thus putatively originating from them. Species transmissibility will be defined as the number of strain transmission events detected for a species divided by the total potential number of strain transmission events based on the presence of a strain‐level profile by StrainPhlAn [40]. We will mainly assess strain transmission across the following modes: related mother‐infant (defined between mothers and their offspring). The transmission between mother‐infant pairs will be evaluated using mothers' stool samples during late pregnancy, which is the closest to delivery time. Further, we will perform de novo assembly and Metapi will be applied [41]. Briefly, the high‐quality reads will be assembled using MEGAHIT [42]. To facilitate genome recovery, reads of samples from the same infants collected at multiple time points will be co‐assembled. Reads will be mapped back to the resulting contigs using minimap with default parameters [43]. Binning of contigs into metagenome‐assembled genomes (MAGs) will be done using two automatic binning programs: MetaBAT2 and VAMB [44, 45]. High‐ (completeness > 90% and contamination < 5%) or medium‐quality (completeness > 50% and contamination < 10%) MAGs (MAGs) will be identified by CheckM, consistent with Minimum Information about a Metagenome‐Assembled Genome (MIMAG) standard [46, 47]. The taxonomic assignment of these representative bacterial species‐level MAGs will be performed by GTDBTk based on the GTDB database [48, 49]. InStrain will be applied to sensitively detect shared microbial strains based on MAGs of species [50]. Apart from the stool samples, the placenta sample and one air swab sample collected during delivery will help to disentangle the true microbial transfer effects from the shared environment between mother and infant.

#### Move forward from correlation to causality

To infer causality from our large‐scale cohort data, we will employ two complementary statistical approaches: (i) Mediation Analysis [51, 52]: We will perform formal causal mediation analysis using structural equation modeling to test whether specific microbial taxa mediate the effect of an exposure (e.g., mode of delivery, diet) on a health outcome (e.g., allergic sensitization, growth metrics). This framework will help delineate potential causal pathways (e.g., Cesarean section → reduced Bifidobacterium → increased asthma risk). (ii) Two‐Sample Mendelian Randomization (MR): We will leverage genetic instruments from large‐scale genome‐wide association studies (GWAS) [52, 53] of gut microbiome traits as proxies for microbial abundance. By applying these instruments to outcome GWAS data, we can estimate the causal effect of the microbiome on child health outcomes while controlling for confounding variables.

Statistical inference will be directly tested and validated through controlled animal experiments designed to establish mechanistic causation. (i) Fecal microbiota transplantation: We will transplant fecal samples from well‐phenotyped MOMMY cohort infants (e.g., from infants who developed atopy vs. those who remained healthy) into germ‐free or antibiotic‐preconditioned mice. A successful transfer of phenotype (e.g., immune dysregulation) would provide direct evidence that the microbial community is causal. (ii) Mono colonization and Defined Consortium Assays: To move beyond community‐level associations and identify specific effector strains, we will: Monocolonize germ‐free mice with individual bacterial species isolated from vertically transmitted lineages (e.g., specific *Bifidobacterium* or *Bacteroides* strains) to assess their unique impact on host immune development. Assemble and administer a defined microbial consortium comprising core vertically transmitted species. This consortium will be used to colonize mice to test the synergistic effect of these strains on promoting early‐life immune maturation and protecting against disease challenges, a strategy that has been employed to induce regulatory T cells [54]. iii) Addressing Translational Feasibility (Colonization Resistance): We acknowledge that colonization resistance is a critical barrier for clinical translation. Ecological principles will be considered in consortium design. For specific pathogen‐free mice, we will precondition mice with antibiotics or use native strains with high fitness and a history of vertical transmission to enhance engraftment success.

## STUDIES DERIVED FROM MOMMY

3

### MOMMY inception cohort: Research novelty and projections

In the MOMMY inception cohort, biosamples including stool, breastmilk, vaginal swab, skin swab, maternal and cord blood have been prospectively collected from 1200 Hong Kong families (mothers, fathers, and offsprings) from pregnancy until the birth of infants followed up to first years of age as of the end of March 2024. In total, >10,000 stool samples from the MOMMY inception cohort families (mother, father, and their infants who reached 1 year old) have been performed in metagenomic sequence (Figure 3B). Leveraging the standardized reproducible body‐wide microbiome sampling SOP, data generation, and computational methods for microbiome analysis and epidemiology interpretation, we will be able to build this platform to integrate microbiome analysis to dissect host microbiome interactions, epigenetics changes, and microbiome trajectories in health and early life.

To maximize the scientific yield, we organized the MOMMY inception cohort into two layers of projects (Figure 4)**:**
*
**(1) Lay the basic infrastructure (i–v):**
* to define the healthy early life microbiome, develop early life microbiome reference database, multi‐omics data set, state‐of‐the‐art computational and statistical tools, environmental exposure (COVID pandemic and nutrition/dietary) assessment; *
**(2) Expand to clinically‐oriented microbiome‐associated conditions (vi–x):**
* Maternal complications: Gestational diabetes mellitus (GDM) and inflammatory bowel disease (IBD); Offspring diseases: pediatric allergic disease and NDD. These studies will follow the dynamics of these conditions through multi‐omic analyses of multiple measurement types over time, including changes in microbial community composition, viromes, metabolomic profiles, gene expression and protein profiles from both host and microbiome, and host‐specific properties such as genetic, epigenomic, along with other study‐specific features. All sequences and multi‐omic data, clinical information, and tools from the MOMMY inception cohort will be housed in the MAGIC Data Coordination Center in Hong Kong.
(i)
*
**MOMMY ‐ HEALTH: Machine Learning Model to Define the Maturation of Microbiome in Chinese Healthy Infants in the First 1000‐day of Life**
* In the first 1000‐day of life, the microbiome of infants goes through significant changes that have long‐term implications for health and disease [55, 56]. Understanding the development of the microbiome in healthy infants is crucial, as it can help identify potential biomarkers, elucidate the dynamics of microbial colonization, and inform the development of interventions to promote optimal microbial growth. Healthy infants are defined based on gestation weeks (full‐term), physical growth (growth *z*‐score between −2 and +2), and the absence of any auto‐immune diseases diagnosed during the specific study periods. In this MOMMY ‐ HEALTH, we will establish a standard reference of the composition of the microbiome throughout the first 1000‐day of life, using metagenomic data generated from the MOMMY inception cohort. Moreover, we will develop a machine learning model to estimate the age of infants based on their microbiome developmental trajectory. Through it, we will identify key microbial community dynamics and patterns associated with microbiome maturation. Any deviation of the microbiome age may indicate potential developmental delays, requiring early intervention such as personalized nutrition and health recommendations. Besides, insights into the impact of key factors in early life, such as breastfeeding, weaning, solid food introduction, and environmental exposures on microbiome maturation are expected. The microbiome‐based machine learning model will lead to a better understanding of the microbiome and its relationship to age and development, which can facilitate the development of new approaches for promoting healthy growth and development in early life.(ii)
*
